# Acknowledgment

It is grateful to thank the Department of Public Health, College of Medicine and Health Sciences, and Wollo University for allowing us to prepare this research proposal.

# Summary

**Background**: Cancer is an emerging public health problem in Ethiopia. A significant proportion of premature cancer deaths are preventable. The socio-economic impact of cancer can be considerably reduced provided that effective interventions are put in place to control risk factors. Text-messaging has been currently targeted as a simple and efficient tool for providing people with health information.

**Objective**: To evaluate the effectiveness of mobile text message in improving behavioral risks of cancer among college students

**Methods**: *Design*: a single-blind, 2-arm randomized controlled trial will be used. *Setting*: the study will be conducted among public colleges in Dessie town, Northeast Ethiopia. *Study population*: students who are studying in all public colleges. *Intervention*: a text message related with cancer risk factors once a day for two months. Control groups will receive general health related text message once a week for two months. *Data*: Socio-demographic, health belief variables and behavioral risk factor of cancer will be collected before and after intervention. Text message will be provided based on health belief model. *Primary outcomes*: cancer risk knowledge score and risk perception will be measured at baseline and 6 month post randomization. *Secondary outcomes*: a change in mean healthy diet score, physical activity level, alcohol intake and tobacco use will be measured at baseline-, 3, and 6 month post-randomization. ***Analysis***: We will compute descriptive statistics for each outcomes pre and post intervention. To test the change in score of HBM, paired t-test will be used. Analysis of Covariance will be used to test over group comparison.

**Work plan and Budget**: The study will be conducted from September 2019 to December 2020. The total required budget is estimated to be **95,243.4 ETB.**

# **Introduction**

Cancer is among the leading causes of premature death worldwide. In 2015, the incidence was estimated to be 17.5 million and was responsible for 8.7 million deaths globally [1]. Previously it was described as a disease of the high-income countries, but now it is also an important public health problem in low- and middle-income countries (LMICs). Lifestyle changes, rapid urbanization, cultural transition, and an increase in life expectancy could attribute to a rise in incidence. From 2005 to 2015, the highest (10–20%) increase in the incidence of cancer was observed in the World Health Organization (WHO) African region [2, 3]. Hence, it imposes an enormous burden on the already overwhelmed health care system of LMICs.

In Ethiopia, 5.8% of the total national mortality in 2015 was due to cancer [3, 4]. In 2015, the numbers of cancer cases were estimated to be 21,563 and 42,722 among males and females respectively [2]. Cancers of the breast, cervix, colorectal cancer, Non-Hodgkin lymphoma (NHL), leukemia, cancers of the prostate, thyroid, lung, stomach, and liver are the most commonly occurring cancers in the country [2-4]. Despite a rise in incidence, cancer still remains among the least public health priorities in Africa, mainly because of the immense burden of communicable diseases along with limited resources [5, 6].

The risk factors for cancer can be broadly categorized into four: behavioral, biological, environmental, and genetic. Behavioral risk factors include tobacco use, harmful use of alcohol, unhealthy diet and physical inactivity [4]. These lifestyle factors are potentially avoidable if appropriate preventive interventions are implemented [1, 7]. Human behavior is a key to the etiology of cancer and presents channels for targeted and sustained intervention [4, 8]. The effect of cancer can be significantly reduced through effective interventions to improve modifiable risk factors, early detection of cases, and appropriate management and care for those with the disease [3].

In Ethiopia cancer screening, diagnosis and management are sub-optimal and population-based data are limited to few cities [3]. Few studies in the country showed poor knowledge towards risk factors and screening were identified as important factors for poor utilization of cancer screening and other prevention services [6, 9, 10]. Thus, behavioral intervention might address a wide variety of key processes and outcomes across the cancer control continuum from prevention to care for survivors [8]. As part of strategy, text messages are currently considered to be the most feasible and widest-reaching mHealth intervention, as they do not require internet or any other advanced facilities [11]. Therefore, this study aimed to measure the effectiveness of text message to improve behavioral risks, which could be helpful to raise cancer awareness and promote cancer prevention and control in this country. We hypothesize that the mobile text messages will improve awareness and risk perception of cancer, ultimately improve the risk reduction behavior. Given the demonstrated effectiveness, delivering the intervention to a larger community might significantly reduce the public health burden of this disease

## Significance of the study

Developing countries including Ethiopia policies and programs are mainly focuses on communicable disease, but know a day’s developing countries are treated with cancer and other non- communicable disease more than communicable disease and face double burden of such problems due to urbanization and changing lifestyle of the community, are a severe threat to our economic development due to the long-term costs of treatment and the negative effects on productivity. Thus this study will give an input via measuring the effectiveness of cost effective mobile text message on reduction of preventable cause of cancer. Measuring the effectiveness of interventions is relevant for policy makers to choice appropriate and easily focus on interventions.

#

# Objective

Our study objective is to assess the effect of cancer specific daily mobile text messages, for early adults, on cancer risk knowledge and risk reduction behaviors such as healthy dietary habit, physical activity, reduction of alcohol consumption and quit smoking, compared to a general health message once a week, North east Ethiopia, 2019

`

#

# Methods

## Study area

The study will be conducted in all public colleges in Dessie town, the administrative town of South Wollo, Northeast Ethiopia. It is 401 kilometer far from Addis Ababa, the capital city of Ethiopia. There are three public colleges in the city, which provides several academic and training services. All public colleges in the city will be included, namely Woizero Siheen Polytechnic College, Dessie College of Teachers Education, and Dessie Health Science college. Woizero Siheen Polytechnic College was established in 1930 and currently provides technical and vocational education and training (TVET) in 5 different campuses: Main Campus (Siheen Campus), Merho Campus, Hotie Campus, Dawdo Campus and Menen (Vocational Campus). The College has more than 325 employees (including administrative and academic staff) and 5975 trainees in regular and night-shift programs. The college is also providing a short-term, non-formal and in-company training. Dessie College of teacher’s education was established in 1980 and has around 107 academic staffs and 1426 students. Dessie Health Science College is not included, as the students in this college expected to have knowledge on risks of cancer and preventive mechanisms.

## Study period

Intervention will be provided from April 01, 2020 to May 30, 2020 G.C.

## Study design

The study will use single blind randomized control trial study design that will assess the effect of mobile text message in behavioral risk factor of cancer among College students and utilize quantitative method of data collection.

## Source population

All Governmental Collage students will be our source population for the intervention and control group

## Study population

All Governmental Collage students will be also our study population for the intervention and control group

## Sample Size Determinations

The sample for this study will be determined using the assumption of superiority trial design to demonstrate the superiority of a new intervention or text message compared to the existing knowledge on cancer prevention. The following formula and assumption will be used to calculate the sample size [12].

[figure not shown]

**Where:**

N=sample size per group;

**δ=**the mean difference of Perceived self-efficacy to adopting behavior between text message and exiting knowledge **δ= 2.9**

S^2^=SD= Pooled standard deviation of both comparison groups S= 6.22, S^2^= 38.74

z= 95% confidence level and 80% power
[figure not shown]
=1.96,
[figure not shown]
=0.845

The total sample size with 10% loss to follow up of study subjects is 160 (80 interventions and 80 controls) students will be selected randomly.

## Sampling procedure

Both Woizero Siheen Poly Technique Collage and Dessie Teachers Training collage will be included in the study. Sample size will be allocated based on proportional to population size. Students’ ID will be obtained from each and used as sampling frame. Then Simple random sampling method will be used to select eligible study subjects. After the baseline assessment, participants will be randomized to either usual care (control) or the text message intervention group in a uniform 1:1 (control: intervention) allocation ratio, using computer-based randomization service.

SRS

SRS

PPS

**160**

##

Figure 1: Schematic presentation of sampling procedure

## Inclusion and exclusion criteria

### Inclusion criteria

Having a personal (own) mobile phone and age >18years

### Exclusion criteria

Self-report of having any cancer, enrolled in another interventional study that use text message as a tool and Dessie Healthy Science Collage students will be excluded from study.

# Study Variables

## Dependent Variables

Behavioral risk factors of cancer

## Independent Variables

Socio-demographic variables: sex, age, marital status, religion

Health belief model (HBM) variables: Perceived susceptibility towards cancer, Perceived severity of cancer, Perceived benefits of adopting behaviors, Perceived barriers to adopting behaviors, Perceived self-efficacy for adopting dietary behaviors ,Internal cues for adopting dietary behaviors.

Others: Parental education, pocket money, collage, year of study, family history of cancer

## Operational definitions

**Intervention group:** a group who received daily cancer specific mobile text message.

**Controls**: comparative group participated in the study and received general healthy mobile text message once a week.

**Behavioral risk factors of cancer:** tobacco use, harmful use of alcohol, unhealthy diet and physical inactivity with a series of items will be used to measure the behavioral outcomes the items in this subscale will be measured on a Likert scale ranging from 1= “I never did” to 6 = “I did every day”.

## Data collection procedure

Self-administered questionnaire will be used to assess baseline and end line data of behavioral risk factors and other variables. To maintain blinding, randomization will occur after the assessment via computer, and then mobile text message will be delivered to participants. Participants in the control group will receive an initial text message welcoming them to the study, then received general healthy text message once a week. The intervention group will receive a text message support program, where they will receive seven messages per week at random times and days for two months. The text messages will be sent to participants in the morning. The principal investigator will be responsible to check the status of each sent item. If a message failed to be delivered, it will be sent again to the recipient. If delivery status keeps to be failed, phone call will be performed to discuss the issue and take measures accordingly. The messages will be prepared and delivered based on the health belief model (HBM). The focus of text messages will be on the prevention of behavioral risk factor of cancer such as harmful use of alcohol, unhealthy diet, tobacco smoking and physical inactivity.

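### No step before randomisation shows that a student's number receives texts, so a non-working number surfaces only after allocation; a cheap delivery check at baseline would prevent most of this

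*Protocol*

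**What the plan says.** - **Entry** (Protocol, Inclusion criteria): "Having a personal (own) mobile phone and age >18years". Nothing is said about whether the recorded number works.
- **Order of events** (Sampling procedure): "After the baseline assessment, participants will be randomized to either usual care (control) or the text message intervention group". Data collection procedure gives the same order: questionnaire, computer randomisation, then messages.
- **First contact** (Data collection procedure): "Participants in the control group will receive an initial text message welcoming them to the study", followed by weekly general-health texts. No welcome text is described for the intervention arm, which goes straight to seven messages a week for two months.
- **Delivery failure** (same section): the principal investigator checks the status of every message sent, and failed messages are sent again. Then: "If delivery status keeps to be failed, phone call will be performed to discuss the issue and take measures accordingly". None of this is limited to one arm. The measures are not specified.
- **Sample size** (Sample Size Determinations): "The total sample size with 10% loss to follow up of study subjects is 160 (80 interventions and 80 controls) students". The 10% allowance is for loss to follow-up, not for texts that never arrive.

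**The concern.** The text message is the whole intervention. The protocol foresees that some numbers will keep failing, but it can learn this only after allocation, when a student can no longer be replaced without risking bias.

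The written remedy for persistent failure is a call to the same phone. That may help when a phone was switched off. It does not obviously help when the number was taken down wrongly or is out of service.

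Such a student may still complete the self-administered endline questionnaire, so the loss-to-follow-up allowance does not cover the case. If analysed as randomised, an unreached intervention student contributes no effect. If set aside instead, the comparison loses the protection of randomisation. The Operational definitions section leaves room for that, because it describes the intervention group by what was received rather than by allocation. An unreached control matters less, since that student misses only weekly general-health texts.

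**Working it through.** **Inputs.** From Sample Size Determinations: difference δ = 2.9; "S= 6.22, S^2^= 38.74"; "z= 95% confidence level and 80% power", with z-values 1.96 and 0.845; 80 per arm including 10% loss. From Sampling procedure: 1:1 allocation. Assumed, because the protocol gives no value: u, the share of intervention students never reached but still analysed.

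**Step 1: reproduce the plan's figure.** The formula image is not shown, so I use the standard one for two means:

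n = 2S²(1.96 + 0.845)²/δ² = 2 × 6.22² × 2.805²/2.9² = 72.4 per arm.

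With 10% added, 72.4 × 1.1 = 79.6, which rounds up to 80 per arm and 160 in total. The stated figure reproduces. (6.22² is 38.69 rather than 38.74; the difference is immaterial.)

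**Step 2: number analysed.** 80 × 0.90 = 72 per arm.

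**Step 3: dilution.** If a share u of the intervention arm has no effect, the expected difference is 2.9 × (1 − u). The SD is held at 6.22. Power is for a two-sided two-sample t-test at 5% with 72 per arm.

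| u (assumed) | Expected difference | Power |
|---|---|---|
| 0% | 2.900 | 79.3% |
| 2% | 2.842 | 77.7% |
| 5% | 2.755 | 75.2% |
| 10% | 2.610 | 70.6% |
| 20% | 2.320 | 60.4% |

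A normal approximation gives values about half a point higher (79.9% at u = 0, 71.1% at 10%) and the same decline.

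**Step 4: what u means in students.** Of the 72 analysed in the intervention arm, 2% is between one and two students (1.4), 5% about four (3.6), and 10% about seven (7.2).

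**Step 5: message budget.** The Budget Plan pays for 100 × 60 = 6,000 texts at 50 cents, or 3,000 ETB. Scheduled messages are about 80 × 60 + 80 × 9 = 5,520, taking two months as 60 days and about nine weekly texts. Adding 160 welcome texts gives 5,680, which leaves 320 for re-sends and replacements. The 160 texts cost 160 × 0.50 = 80 ETB.

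**The case against.** The strongest reply is that the delivery procedure already deals with this. Every sent item is checked in both arms, failures are re-sent, a call follows, and the open-ended measures could include finding the student at college, since participants come from ID lists at two named colleges. Only those still unreachable after all of that dilute the effect, and nothing in the protocol suggests they are many. This stands, and it is why the point is minor.

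Four stronger readings are tempting and are not supported.

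- *Only controls have their numbers tested.* The welcome text is not described as a test, and the first daily message tests an intervention number just as well.
- *Students with failing numbers receive nothing.* That is true only of those whom the re-send, the call and the further measures all fail to rescue.
- *Some 60 messages against 9 make detection unequal.* A dead number fails at first contact in either arm. The imbalance applies only to intermittent failures, and those students do receive texts.
- *Unreachable students will be removed or replaced after randomisation.* No section says so; the protocol only leaves it open.

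Two cautions about the figures also stand. The difference of 2.9 is taken from a cited text-messaging study, so it may already include some non-receipt. Unreachable students may also overlap with the 10% lost to follow-up. Either would make the losses in the table too large.

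It can also be argued that excluding undeliverable numbers narrows an effectiveness question. That carries little weight here, because owning a phone is already an entry criterion. A single test cannot prevent failures that arise later in the two months, which is a real limit of the fix.

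**Conclusion.** The point holds in a limited form. Entry rests on phone ownership, every text follows randomisation, and a number that never worked is discovered only when the student is already allocated. Existing procedures will recover some of these students in both arms. Those they do not recover in the intervention arm reduce the expected difference in proportion to their share.

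Under the assumptions above (no effect in unreached students, unchanged SD, 72 analysed per arm), the loss of power is about 1.5 points at 2%, 4 points at 5% and 9 points at 10%. The 20% row needs one intervention student in five to stay unreachable after re-sending and calling, and nothing in the protocol supports a rate that high. Because the protocol gives no rate, the figures show sensitivity and are not a forecast.

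A reader might infer that the trial is undersized. It is not on this ground: 160 follows from the stated inputs. This is an avoidable weakness in the order of steps, worth correcting because the correction is cheap.

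**What to change.** In Data collection procedure and Sampling procedure:

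1. After the baseline questionnaire and before randomisation, send the same welcome text to every consenting student, in place of the control-only welcome text.
2. Where it is not delivered, correct the number with the student. If it cannot be corrected, draw the next student from the ID list.
3. Add confirmed delivery of the welcome text to the inclusion criteria and randomise only those students, so that all 80 + 80 are reachable at allocation.
4. State that every randomised student stays in the allocated arm for analysis even if later messages fail, and word the operational definition of the intervention group by allocation.
5. Say what the measures after a failed phone call consist of, identically for both arms.

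**Cost.** About 80 ETB for 160 texts, inside the existing budget of 6,000 messages. The net addition is about half that, since the 80 control welcome texts are replaced. There is also a short delay between baseline and randomisation, and a few extra consents and baseline questionnaires for replacements. The sample size does not change.

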### Outcome measures

All the primary and secondary outcomes will be measured at baseline and at 6 month post-randomization. Self-administered questionnaire will be used to collect the baseline and post-intervention socio-demographic characteristics, knowledge towards cancer, risk perception, and lifestyle behaviors.

### Primary outcomes

The primary outcomes for this trial are knowledge of behavioral risks of cancer and risk perception. To assess the risk perception of cancer, we will obtain data on the health belief model variables: Perceived susceptibility towards cancer ( e.g. You perceived that you will get risk of developing cancer at any time of your life), Perceived severity of cancer (e.g. “Cancer is fatal, and its complication are dangerous/severe in life”) Perceived benefits of adopting behaviors (e.g. “Having a healthy nutrition would decrease the probability of many type of cancers”) Perceived barriers to adopting behaviors (e.g. “My monthly income is insufficient to take the recommended diet for the prevention of cancer”), Perceived self-efficacy for adopting dietary behaviors (e.g. “I am confident that I can prevent cancer through healthy lifestyle”) Internal cues for adopting dietary behaviors (e.g. “when knowing the death of any by cancer, it flips me to perform the preventive behaviors”) the items of this subscale will be measured on a Likert scale ranging from 1= “Strongly disagree” to 5 = “Strongly agree”.

### Secondary outcomes

**Dietary habit**: will be measured using the food frequency questionnaire, the type and frequency of food items a participant consumed in the past 1 month.

**Physical activity level**: will be measured using International Physical Activity Questionnaires short form (IPAQ-S). The questions will ask the number of days and time participants spent doing vigorous physical activity, moderate physical activity, walking, and sitting in the last 7 days.

**Alcohol intake**: will be assessed using a tool adapted from the National Institute on Alcohol Abuse and Alcoholism (NIAAA), which we will use to assess participants consumption in the past 1 month.

**Tobacco use**: will be assessed using a series of questions adapted from the World Health Organization (WHO), which will assess the duration, quantity and frequency of smoking.

## Data quality control

Validity of the items will be measured by an expert panel of specialists in health education and nutrition. They will judge about the necessity and relevance of the scale items. To control the data quality all data collectors will be trained for two days. Supervisors will monitor data collection process and the principal investigator will visit frequently. The questionnaire will be first prepared in English language and translated to Amharic and again re-translated in to English by another person to check for consistency. 10% of the questionnaire will be pretested. Internal consistency will be checked using SPSS version 23 until the acceptable level reached. Completeness of the collected data will be checked during data collection by the supervisors and the principal investigators.

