# Budget Plan

Table 2: Budget break down

| **Baseline assessment** | | | **Working**  **Days** | | | | **Per diem** | | | | **No. of workers** | **Costs in ETB** | | | **Total** | | |  |
| --- | --- | --- | --- | --- | --- | --- | --- | --- | --- | --- | --- | --- | --- | --- | --- | --- | --- | --- |
| Perdiem for the researchers/PI | | | | 7 days | | | | | 192 | 3 | | | | 3x7x192 | | 4302 | | |
| Perdiem for supervisor | | | | 4 days | | | | | 192 | 2 | | | | 2x4x192 | | 1536 | | |
| Perdiem for trainer | | | | 7 days | | | | | 192 | 2 | | | | 2x7x192 | | 2688 | | |
| Perdiem for trainee | | | | 4 days | | | | | 192 | 6 | | | | 6x4x192 | | 4608 | | |
| Perdiem for data collectors | | | | 10 days | | | | | 192 | 4 | | | | 4x10x192 | | 7680 | | |
| Perdiem for data analysis and interpretation | | | | 10 days | | | | | 192 | 3 | | | | 4x10x192 | | 5760 | | |
|  | | | | | | | **Sub total** | | | | | 26,574 | | | | | |  |
| **End line assessment** | | | | | | | | | | | | | | | | | |  |
| Perdiem for the researchers/PI | | | | | 7 days | | | 192 | | 3 | | | 3x7x192 | | | | 4302 |  |
| Perdiem for supervisor | | | | | 4 days | | | 192 | | 2 | | | 2x4x192 | | | | 1536 |  |
| Perdiem for trainer | | | | | 7 days | | | 192 | | 2 | | | 2x7x192 | | | | 2688 |  |
| Perdiem for trainee | | | | | 4 days | | | 192 | | 6 | | | 6x4x192 | | | | 4608 |  |
| Perdiem for data collectors | | | | | 10 days | | | 192 | | 4 | | | 4x10x192 | | | | 7680 |  |
| Perdiem for data analysis and interpretation | | | | | 10 days | | | 192 | | 3 | | | 4x10x192 | | | | 5760 |  |
|  | | | | | | | | **Sub total** | | | | | 26,574 | | | | |  |
| **Follow up** | | | | | | | | | | | | | | | | | |  |
| Perdiem for the PI for follow up ,  and write up | | 60  Days | | | | | | 192 | | 3 | | | 3x60x192 | | 34,560 | | |  |
| Text message | | 60 Days | | | | | | 50 cent | | 100 | | | 100x60x50 | | 3000 | | |  |
|  | | | | | | **Sub total** | | | | | | | | 37,560 | | | | |
| 5% Contingency | **4535.4** | | | | | | | | | | | | | | | | | |
| Grand total | **95,243.4** | | | | | | | | | | | | | | | | | |

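### Tracking messages reveals the arm, and the role that tracks them also visits and checks data collection, with nothing shielding the 6-month wave

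*Protocol*

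**What the plan says.** Data collection procedure assigns message tracking to one role: "The principal investigator will be responsible to check the status of each sent item". The schedules differ by arm. For the intervention group, "they will receive seven messages per week at random times and days for two months"; controls get a welcome text and "then received general healthy text message once a week". If resending does not help, "If delivery status keeps to be failed, phone call will be performed to discuss the issue and take measures accordingly".

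Data quality control then covers fieldwork: "Supervisors will monitor data collection process and the principal investigator will visit frequently", and "Completeness of the collected data will be checked during data collection by the supervisors and the principal investigators". Neither sentence separates baseline from end line. Data collection procedure and Outcome measures use a self-administered questionnaire at both baseline and 6 months.

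On blinding, Study design says: "The study will use single blind randomized control trial study design". The Summary uses the same label. Neither says who is blinded. The one measure described, in Data collection procedure, is that randomisation follows the assessment.

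**The concern.** Randomising after the assessment means that nobody can know the arm while baseline data are collected. It does nothing for the 6-month wave, when two months of messages have been sent and tracked. At that wave, the role that followed the messages is also expected on site and has a part in checking the forms.

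The primary outcomes are knowledge and health-belief answers, and the secondary outcomes are self-reported diet, activity, alcohol and tobacco. Answers of this kind, and the choice to leave an item blank, can respond to who is present and to queries about gaps. If that response differs by arm, the analysis of covariance named for the between-group comparison will count it as intervention effect.

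This is separate from students knowing which messages they themselves received. That knowledge cannot be removed. The staff route exists only because of how duties are assigned.

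**Working it through.** **1. Set the duties side by side.**

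| Step | Who | Section | Arm visible? |
|---|---|---|---|
| Baseline questionnaire | Supervisors and investigators check | Data quality control | No, randomisation comes later |
| Delivery status of each message | Principal investigator | Data collection procedure | Yes, seven a week against one |
| Call after persistent failure | Not named | Data collection procedure | Depends on the caller |
| 6-month questionnaire | Supervisors and investigators check; principal investigator visits | Data quality control | Yes, for anyone who has seen the log |

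No section keeps the second and fourth rows apart, and no blinding measure covers the fourth.

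**2. Check the staffing in the Budget Plan, End line assessment.** The row "Perdiem for supervisor" gives 2 people × 4 days = 8 person-days. Data collectors: 4 × 10 = 40 person-days. Researchers/PI: 3 × 7 = 21 person-days, with no task stated. So investigators are paid at end line, and other staff are paid for the same wave. The supervisors' days alone do not span the ten collection days.

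**3. Reproduce the plan's own figure.** Inputs from Sample Size Determinations: difference 2.9, SD 6.22, z values 1.96 and 0.845, 10% loss, 80 per arm.

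n = 2 × (6.22 × 2.805 / 2.9)² = 72.4 per arm. Allowing for loss, 72.4 / 0.9 = 80.4 and 72.4 × 1.1 = 79.6. The stated 80 per arm reproduces.

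**4. Illustrate what a differential shift would do.** The documents give no size for such a shift, so b = 0.05, 0.10 and 0.20 SD are assumed. Completers per arm: 80 × 0.9 = 72. With no true effect, the two-sided rejection rate is

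P(Z > 1.96 − b√(72/2)) + P(Z < −1.96 − b√(72/2)), where √(72/2) = 6.

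| Assumed b | Points (b × 6.22) | Share of 2.9 | False-positive rate |
|---|---|---|---|
| 0 | 0 | 0% | 5.0% |
| 0.05 SD | 0.31 | 11% | 6.0% |
| 0.10 SD | 0.62 | 21% | 9.2% |
| 0.20 SD | 1.24 | 43% | 22.4% |

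These rates only restate the assumed input. They use the SD of the self-efficacy score and do not carry over to knowledge or behaviour.

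**The case against.** The strongest reply is that the route is narrow. Students complete the forms themselves, no staff member rates anyone, and the stated check is for completeness, not content. Bias needs an investigator who recognises a student's arm and acts on it, or students who react differently by arm to that person's presence. Students' own awareness of their messages remains whatever is done, so the fix removes only an increment of unknown size. All of this stands, and it limits the point to possible influence.

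A reader might infer more than the text supports:

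- *That one person holds both tasks.* The completeness check is given to investigators in the plural, and the budget lists three researchers/PI. Different people could hold the two tasks. The Protocol does not separate them, but it does not fix one individual either.
- *That the investigator phones students.* The sentence on calls names no caller.
- *That calls fall mainly on the daily arm.* Any percentage needs a failure rate, which is not given, and failures independent between messages. A call follows only persistent failure, which more plausibly belongs to a phone or number and so clusters within a student. No figure can be defended.
- *That forms are queried while students answer.* The text refers to the completeness of collected data, checked during the fieldwork period.
- *That the investigator will know the arm of the student at hand.* The log shows the arm by recipient. Whether a visitor could match it to a student or form is not stated.
- *That the Protocol breaks its own blinding.* If the label refers to students, no staff blinding was promised. The label is unclear, and the staff route is open on either reading.

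**Conclusion.** The point holds as a gap in how duties are assigned. Tracking messages reveals the arm, the same role visits and checks during data collection, no exception is made for 6 months, and the only blinding measure ends at baseline. That arm knowledge follows from tracking is an inference from the two schedules, though a strong one.

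The consequence is an avoidable possible bias in self-reported end-line answers or item completion. Its size is unknown. The range of 6% to 22% rests wholly on the assumed shifts of 0.05 to 0.20 SD and is not an estimate for this trial. The sample size is not affected. The change should be made because it is cheap and because subjective outcomes have little other protection.

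**What to change.** 1. **Study design:** state who is blinded (students, data collectors, supervisors or analysts), and use the same statement in the Summary.
2. **Data quality control:** leave the baseline arrangements as they are. For the 6-month wave, state that on-site supervision and completeness checks are done only by the budgeted supervisors and data collectors, who have no access to the message log or the allocation list. State also that any investigator who tracked messages does not attend end-line sessions or handle forms until data entry is closed. If the 3-month measurement in the Summary is kept, apply the same rule there.

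Cost: a few sentences and no new posts. The supervisors' 4 days must be scheduled across the 10 data-collection days, with data collectors covering the rest. The investigator loses direct oversight of end-line quality. An investigator who has had no part in tracking and no sight of the log would not be barred by this wording from attending, but would still not carry out the checks.
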